### Statistical methods

Analysis of effectiveness will be made followed by the intention to treat analysis. Descriptive statistics will be computed as customary [25,26]. Control and intervention groups will be checked for health and outcome measures and a baseline comparability analysis of the CG and IG in relation to the variables studied, will be carried out. An t-Student test or ANOVA will be used in the comparison of means if the variables follow a normal distribution and the U of Mann Whitney if they do not. For the other dimensions of the analysis, a covariance analysis (ANCOVA) for repeated measures will be carried out.

Multi-variate analysis will evaluate the change in the time of the described dependent variables, and comparisons between the CG and IG will be established. To do this multilevel linear models will be adjusted, one for each dependent variable. In the first level the individual path or the evolution of each individual over a long period of time (pre-post intervention, 3, 6 and 12 month follow- up) will be modelled. In the second level it will be adjusted according to the variables that refer to the individual; the intervention variable will be added (intervention or control) to the independent variables described earlier.

The level of statistical significance will be set at 0.05, and all tests will be two-tailed. Statistical analyses will be conducted using SPSS, version 17.0 (SPSS Inc, Chicago, IL).

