### Recruitment process and randomisation

Recruitment will take place in 13 PHC in different regions of Spain (Barcelona, Lleida, Zaragoza and Almeria). Primary health care professionals, who were selected on a voluntary basis from each of the participating centers, were trained. During the recruitment period, the opportunity to participate in the study will be offered at least once a week to all patients with overweight or mild obesity. A total of 30 subjects will be recruited in each PHC. Patients who meet the inclusion criteria and agree to participate will be contacted and informed about how the project will be carried out. All of them will be requested to sign the informed consent form to take part in the study. Demographic and health data will be recorded for all participants.Random sequence generation will be computer-generated by an independent researcher, guaranteeing that the allocation groups remain confidential. Participants will be randomized to intervention group (IG) or control group (CG) after baseline measures assessment. Figure 1 shows the flowchart of participants’ recruitment and trial design.

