### Description of the intervention

#### Intervention group

The intervention will be done according to the patient’s willingness to reduce sitting time (stage of change), and considering whether the subject prefers a more or less intensive intervention: (a) precontemplative (not thinking about change) and contemplative (thinking about change), (b) ready to change with minimum professional support, or (c) ready to change with intensive professional support. All of them will be handed a card with the planned sessions and Mediterranean diet recommendations.

Precontemplative and contemplative patients (a) will be informed of the risks of being 6 or more hours sitting and will be asked about the importance and confidence for change. Ready to change patients (b and c) will be proposed an intervention based on 2–5 meetings (visits face-to-face or phone calls depending on the situation of each professional and patient) with a trained professional during 6 months. On those meetings, the professional will work on finding alternatives to progressively reduce SB by developing the same activities walking.

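### The two-level model has no term for centre or delivering professional, so the standard error of the group effect is too small if intervention-arm outcomes cluster by deliverer or the effect varies by centre

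*Protocol article*

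**What the plan says.** The Statistical methods section of the protocol article plans a separate model for each outcome: "To do this multilevel linear models will be adjusted, one for each dependent variable". The first level is the repeated measurements: "In the first level the individual path or the evolution of each individual over a long period of time". The second level is the person: "In the second level it will be adjusted according to the variables that refer to the individual", and there "the intervention variable will be added (intervention or control) to the independent variables described earlier". No further level is named. The individual data listed under Other specific objectives (age, marital status, education, blood pressure, BMI, associated pathologies) do not include centre. The t-test, Mann-Whitney test and repeated-measures ANCOVA are also described without a centre term.

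On the design, the section on recruitment and randomisation says "Recruitment will take place in 13 PHC in different regions of Spain". The professionals were "selected on a voluntary basis from each of the participating centers, were trained". The Intervention group section offers participants who are ready to change 2 to 5 contacts "with a trained professional during 6 months", in a format that depends on the professional and the patient. Controls receive usual care and a diet pamphlet. Randomisation is by individual.

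**The concern.** The two arms differ in how they are grouped. Intervention participants who are ready to change work with a particular professional over six months, and the number and form of contacts can vary between professionals. Their outcomes may therefore be correlated through that professional, while controls have no comparable exposure. This is a partially nested design. Individual randomisation does not remove such correlation, and a model that stops at the person treats these participants as independent.

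At stake is the standard error of the group effect, and with it the width of the confidence interval and the real size of a nominal 5% test. A lesser matter is precision: if sitting time differs between centres, a model without centre leaves that variation in the residual.

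**Working it through.** The plan states no figure for clustering, so there is none to reproduce. The check asks in which direction, and by how much, the two-level standard error (SE) would be wrong.

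**Inputs from the article**
- 232 participants, 116 per arm (Sample size), before dropout and without the fibromyalgia subjects
- 13 centres (recruitment section)
- two-sided alpha 0.05 (Sample size; Statistical methods)

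**Assumed, because the article does not give them**
- ICC: 0.02, 0.05, 0.10
- deliverers per centre: one or two
- every intervention participant is exposed to the deliverer
- clusters of equal size

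**Case A: a centre effect shared by both arms.** With 1:1 allocation within each centre, the effect cancels from the group difference, but the two-level model still counts it as residual variance. True SE / model SE = √(1 − ICC) = 0.990, 0.975, 0.949. The model SE is slightly too large, which is conservative. In a simulation with no treatment effect (13 centres, 232 participants, 6,000 runs, simple comparison of arm means), ICC 0.05 gave a type I error of 0.044 with allocation balanced within centre and 0.049 with simple randomisation.

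**Case B: clustering in the intervention arm only.** With m intervention participants per deliverer:
- design effect in that arm, DE = 1 + (m − 1) × ICC
- SE ratio (true / model) = √((DE + 1)/2), because the control arm has a design effect of 1
- type I error = 2 × (1 − Φ(1.96 / SE ratio))

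One deliverer per centre, m = 116/13 = 8.92:

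| ICC | DE | SE ratio | Type I error |
|---|---|---|---|
| 0.02 | 1.158 | 1.039 | 5.9% |
| 0.05 | 1.396 | 1.095 | 7.3% |
| 0.10 | 1.792 | 1.182 | 9.7% |

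Two deliverers per centre, m = 116/26 = 4.46:

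| ICC | DE | SE ratio | Type I error |
|---|---|---|---|
| 0.02 | 1.069 | 1.017 | 5.4% |
| 0.05 | 1.173 | 1.042 | 6.0% |
| 0.10 | 1.346 | 1.083 | 7.0% |

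The same simulation with intervention-arm ICC 0.05 and one cluster per centre gave a type I error of 0.075 (balanced within centre) and 0.073 (simple). The empirical SE was 0.143 to 0.145 against a model SE of 0.131. The formula and the simulation agree.

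**Cluster size.** The recruitment section also says "A total of 30 subjects will be recruited in each PHC". That would make 13 × 30 = 390, which does not match 232 and is a separate matter. Taken at face value with one deliverer per centre, m = 15, and ICC 0.05 and 0.10 give SE ratios of 1.16 and 1.30 and type I errors of about 9.2% and 13.3%. So m is uncertain in both directions.

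**The case against.** Four objections deserve an answer.

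1. **Individual randomisation.** A reader might infer that leaving out 13 centres must understate the SE, as it would in a cluster-randomised trial, where the design effect at ICC 0.05 would be 1 + (17.85 − 1) × 0.05 = 1.84. The document does not support that. Centre effects common to both arms do not inflate the error (Case A). Only deliverer clustering in one arm, or a group effect that varies by centre, does. This objection stands and limits the point.

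2. **The size rests on assumptions.** The article refers to professionals in the plural and gives no number per centre. With three per centre (m = 116/39 = 2.97) and ICC 0.05, the type I error is only 5.6%. Participants not yet ready to change are only informed of the risks and asked about importance and confidence, so part of the intervention arm has little exposure to a deliverer. If the intervention changed nobody's outcome, there would be no deliverer variance and no inflation from it; the inflation needs deliverer effects that exist but average to zero. All this stands. A reader should not take from the tables that the type I error is above 5% as a fact.

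3. **Randomisation.** One might also infer that allocation does not balance on centre. The article says only that the sequence is computer-generated by an independent researcher. Stratification is neither stated nor excluded, and a condensed article may omit it. Nothing here depends on it.

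4. **Detail left to a fuller document.** A condensed article need not give the whole random-effects structure. Here, however, the levels are enumerated and end at the person. An analyst following the text would fit two levels, so this objection does not remove the point.

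**Conclusion.** The point holds in a limited form. The stated model omits a known feature of the design: professionals at 13 centres deliver the intervention to one arm. The consequence is conditional. If intervention-arm outcomes cluster by deliverer, or the group effect varies by centre, the two-level SE is too small. At 232 participants and assumed ICCs of 0.02 to 0.10, the true SE would be about 4% to 18% larger than the model's with one deliverer per centre (type I error about 5.9% to 9.7%), and about 2% to 8% larger with two (about 5.4% to 7.0%). If the only clustering is a centre effect shared by both arms, the loss is one of precision, and under balance within centre the test is slightly conservative. The article's figures cannot settle which case applies. The issue is moderate, and it should be settled before the data are analysed.

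**What to change.** In Statistical methods, add the primary care centre, as a random intercept or fixed effect, to every between-group model. Record which professional delivers the intervention to each participant. Fit a random effect for that professional in the intervention arm, or a centre-by-group random effect, with small-sample degrees of freedom, at least as a pre-specified sensitivity analysis. A centre intercept alone recovers precision but does not address the component that makes the SE too small.

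The cost is analysis wording plus one recorded item, the deliverer's identity; the article does not say that this is captured, and recruiting centre should be confirmed as a field too. No extra participants or visits are needed. The statistical price is wider intervals from the model with the random group effect. With 13 clusters and about 12 degrees of freedom the critical value is 2.18 instead of 1.96, a factor of 1.11. With the SE ratio of 1.095 at ICC 0.05, intervals would be about 1.11 × 1.095 ≈ 1.22 times as wide, so roughly 20% wider.

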### Ethical approval

The study will be carried out according to the principles of the “Declaration of Helsinki” and subsequent revisions [27]. This study was reviewed and approved by the Clinical Investigation Ethics Committee of the IDIAP Jordi Gol, located in Barcelona. The participation of the subjects is strictly voluntary and withdrawal will not have any consequence on the management of their illness which will be carried out by their doctor strictly following the accepted international norms. The data will be treated with utmost confidentiality according to the Organic Law which regulates the confidentiality of computerized data (Protection of personal information Law 15/1999), and will be used exclusively for the purposes of this scientific investigation.

## Discussion

Sedentary behaviour (SB) in general and sitting time in particular is increasingly recognised as a health risk behaviour. Evidence suggests that SB is associated with increased cardiovascular disease, diabetes, obesity and mortality independent from physical activity (PA) level [6,7]. Overweight and obese people are more sedentary (they spend more hours sitting each day). In addition, they have shown poor rates of change and adherence to PA [28,29]. Thus, prevention and reduction of obesity should be a public health priority, and reducing SB could be an appropriate strategy [3].

Primary care centers (PHC) are an ideal setting to identify adults who spend extended periods of daily sitting, and to treat people with overweight and mild obesity. Furthermore, are a key scene to initiate a cost-effective SB intervention. PHC practitioners can play an important role in population health throughout lifestyle promotion [30]. A high percentage of the population visit their primary care professional at least once a year [31] and tend to have confidence with them. Research has shown that PHC practitioners’ suggestions have a high impact in patients’ everyday life [32].

Encouraging overweight and mild obese patients to reduce sitting time could be the first step to increase their daily caloric expenditure. There are few randomized controlled trials (RCT) that had assessed the impact of interventions on the reduction in daily sitting time. Additionally, these studies have included small samples. RCT to reduce SB in sedentary patients based on objective measures to assess daily sitting time are needed.

SEDESTACTIV is a RCT based on a PHC intervention carried out by a healthcare practitioner to assess whether a sustained reduction of sitting time among overweight and mild obese adults is possible, and if so, to evaluate the effectiveness in determining health benefits among the studied population. The design of the SEDESTACTIV study takes advantage of the direct contact and accessibility of PHC with patients.Figure 1 shows the consolidated standards of reporting trials (CONSORT) flow diagram.

## Abbreviations

WHO: World Health Organization; PA: Physical activity; SB: Sedentary behavior; METs: Metabolic Equivalent Units; RCT: Randomized controlled trial; PHC: Primary health care; IDIAP Jordi Gol: Primary Care Research Institute Jordi Gol; CONSORT: Consolidated Standards of Reporting Trials; BMI: Body mass index; IG: Intervention group; CG: Control group; OSPAQ: Occupational Sitting & Physical Activity Questionnaire; CBPAAT: Catalan version of Brief Physical Activity Assessment Tool; HDL: High-density lipoprotein; LDL: Low-density lipoprotein.
